## Statistics

### Sample size calculation

Sample size calculations are based on the Log-rank test for superiority of the experimental arm over the comparator arm in LRC-survival over two years. The two-year LRC-survival is expected to be about 60% in the comparator group and about 75% in the experimental group. When the sample size in each group is 125, the one sided Log-rank test will have power of about 80% to detect the assumed difference at the 0.05 level. Therefore, 250 patients need to be recruited in the trial, 125 in each arm.

Due to missing alternative therapy concepts in non-resectable LAHNSCC, the expected compliance rate will be over 95%. Missing values will be conservatively treated: In the control arm, missing values will be imputed by the longest observed loco-regional survival time. In the experimental arm, missing values will be set to the time of censoring.

Because of the pre-study requirements of the BfS the pre-study will include 20 patients. These 20 patients are on top of the calculated 250 patients for the whole trial.

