### Statistical methods

#### Primary efficacy endpoint analysis for the main part of the trial

The primary efficacy endpoint of the trial, LRC-survival over two years, will be tested for superiority of the experimental arm over the comparator arm using the one-sided Log-rank test at the 0.05 significance level on the ITT set. LRC-survival is defined as time to local relapse or death calculated from start of radiotherapy.

The corresponding hypotheses are:

H0: Se(t) ≤ Sc(t) vs. Ha: Se(t) > Sc(t),

Se and Sc denote the two-year LRC-survival in the experimental arm and in the control arm respectively.

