#### Missing data

Missing values will be conservatively imputed for the assessment of the primary endpoint: In the control arm, missing values will be imputed by the longest observed loco-regional survival time. In the experimental arm, missing values will be set to the time of censoring. The primary endpoint will also be analyzed as a secondary endpoint without imputation. Imputation is not performed for the secondary endpoints.

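### The primary endpoint is timed from the start of radiotherapy but tested on the ITT set, so a randomised patient who never starts has no defined survival time

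*Protocol article*

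**What the plan says.** The section *Primary efficacy endpoint analysis for the main part of the trial* names the test as a "one-sided Log-rank test at the 0.05 significance level on the ITT set". The next sentence defines the endpoint: "LRC-survival is defined as time to local relapse or death calculated from start of radiotherapy". The words at issue are "calculated from start of radiotherapy".

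The article gives one rule for a primary value that is not available. It appears under *Sample size calculation* and again under *Missing data*, and it differs by arm:
- Control: "In the control arm, missing values will be imputed by the longest observed loco-regional survival time".
- Experimental: "In the experimental arm, missing values will be set to the time of censoring".

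The *Missing data* section adds a second analysis: "The primary endpoint will also be analyzed as a secondary endpoint without imputation".

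On how often this might arise, *Sample size calculation* says only that "the expected compliance rate will be over 95" per cent. It does not say what compliance covers. The article does not define the ITT set further and does not mention randomised patients who never begin radiotherapy.

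**The concern.** An ITT comparison needs a time origin that exists for every randomised patient. The first fraction is not such an origin. It comes after allocation, because the arms differ from the first fraction (2.3 Gy against 2.0 Gy in the abstract's Methods) and the SIB 80.5 volume is drawn only for arm A.

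Death is part of the endpoint. A randomised patient who dies before radiotherapy has therefore had a primary event, yet the definition gives no time at which to place it. The same holds for a relapse or withdrawal in that interval.

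Two things are at stake. If these patients are left out, the primary result is a treated-patient comparison presented as ITT. If they are imputed, their result depends on the arm and not on what happened to them. In either case the choice could be made after outcomes are known, which a primary definition should prevent.

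**Working it through.** **1. Do the stated rules fit each other?**

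| Randomised patient | Time under the stated definition |
|---|---|
| Starts radiotherapy | Defined |
| Dies before the first fraction | Event known, but no origin to time it from |
| Relapses before the first fraction and never starts | Event known, but no origin |
| Withdraws before the first fraction | No origin and no censoring time |

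The ITT set includes all four rows; the endpoint exists only for the first. The experimental-arm imputation rule does not close the gap, because a censoring time also needs an origin. The analysis without imputation does not close it either, because these patients still have no time and leave the comparison.

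**2. The plan's own power figure.** Inputs from *Sample size calculation*: 125 per arm, 60% against 75% at two years, one-sided 0.05, power about 80%.
- Hazard ratio = ln(0.75)/ln(0.60) = 0.563.
- Expected events by two years = 125 × (0.40 + 0.25) = 81.25.
- Freedman: √81.25 × (1 − 0.563)/(1 + 0.563) − 1.645 ≈ 0.874, power 80.9%.
- Schoenfeld: √81.25/2 × |ln 0.563| − 1.645 ≈ 0.943, power 82.7%.

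The stated power reproduces, so the sample size is not in question.

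**3. Size if never-starters are imputed.** *Assumption:* k per arm, from 0 to 6. The upper end reads the whole 5% shortfall in compliance as never starting (0.05 × 125 = 6.25). The article does not say this.

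If k control patients count as event-free, apparent control two-year LRC-survival = (k + (125 − k) × 0.60)/125 = 0.60 + 0.40k/125:
- k = 0: 60.0%
- k = 3: 61.0%
- k = 6: 61.9%

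**4. Effect on the test.** Log-rank simulation with exponential times, a 24-month cut-off and 8,000 runs per scenario. Further assumptions: never-starting is unrelated to prognosis, imputed control patients are event-free at 24 months, and imputed experimental patients are censored at time 0.

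| Never-starters (control, experimental) | Handling | Power | One-sided type I error |
|---|---|---|---|
| 0, 0 | all timed | 82.1% | not run |
| 3, 3 | imputed | 76.7% | about 3.4% |
| 6, 6 | imputed | 72.5% | about 2.5% |
| 6, 0 | imputed | 73.0% | about 2.3% |
| 0, 6 | imputed | 81.4% | about 5.5% |
| 6, 6 | left out | 79.9% | not run |

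The Monte Carlo standard error is about √(0.8 × 0.2/8000) = 0.4 points for power and √(0.05 × 0.95/8000) = 0.24 points for type I error. The 5.5% is thus about two standard errors from 5%. Patients censored at time 0 carry no information, so no true inflation is expected there.

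**5. What belongs to which rule.** Leaving out six per arm costs 82.1 − 79.9 = 2.2 points of power. Imputing them costs a further 79.9 − 72.5 = 7.4 points, nearly all from the control half of the rule (73.0% with control never-starters only). Most of the loss is therefore due to the arm-specific imputation, which the missing time origin can trigger but does not itself cause.

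**The case against.** The strongest reply is that only the mismatch between ITT and the time origin is in the text, and that the rest is inference. Much of this stands.

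- **Never-starters are not called missing.** A reader might infer that control deaths before treatment are turned into the longest survival time in the trial. The article does not say so. Such a death has a known date and death counts as an event, so a sensible analyst might count it. What stands is that the stated definition does not say how.
- **No number is given.** A reader might take the compliance statement to mean that up to 5% never start. It is an expectation, its scope is undefined, and the reason given (few alternative treatments) suggests that most patients will start.
- **Arm-dependent delay.** A reader might infer that the extra dose level delays arm A. No interval from randomisation to first fraction is given, and both arms use SIB-IMRT and share the SIB 70 and SIB 56 volumes. An assumed one-week difference would matter little: the control hazard is −ln(0.60)/24 = 0.0213 per month, and 0.60 × 0.0213 × 0.23 month is about 0.3 points.
- **Direction.** The imputation is labelled conservative and does penalise the experimental arm. A claim of inflated false positives would be wrong under the assumptions used here.
- **The figures mainly measure another rule.** A control patient who withdraws before treatment and is lost to follow-up could still be imputed after the origin is moved, unless the censoring rule is also stated.
- **The full protocol may define ITT.** It may, but the time origin itself is stated in the article and does not fit the set named beside it.

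**Conclusion.** The point holds as an inconsistency between two stated rules: an ITT set paired with an origin that not every randomised patient has. It does not show that the planned result is biased by a known amount.

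The practical effect is nil if everyone starts. At the assumed upper end of 6 per arm, all imputed and unrelated to prognosis, control two-year LRC-survival would read 61.9% instead of 60%. Power would be about 73% instead of about 82%, with one-sided type I error of about 2.5%. These figures are conditional, and most of the power loss comes from the imputation rule.

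Nor does the 82% mean that a randomisation origin would restore full power. It assumes that never-starters have the ordinary event times of their arm. If all six per arm were instead immediate events, simulated power would be 76.9%. The reason to change is that the analysis would then match its label and count early events, whatever the power.

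**What to change.** Define LRC-survival as time from the date of randomisation for all randomised patients. Count deaths and relapses before radiotherapy as events. Censor patients without an event at their last assessment, or at randomisation if there is none, and say that this applies to patients who never start, so that the arm-specific imputation does not reach them. Keep the radiotherapy origin as a supportive analysis in patients who started.

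The cost is a short amendment to the primary endpoint definition, passed through the usual approvals and made before outcomes are examined by arm. It needs no new assessments and leaves the sample size unchanged. The article does not say that the randomisation date is recorded, but randomising a patient produces one.

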#### Secondary efficacy and safety endpoint analyses

Secondary efficacy and safety endpoints will be analyzed in an explorative manner on a 5% significance level. Kaplan-Meier estimators and life-table methods will be used for the analysis of time-to-event data and life-table data. Cumulative incidence estimators will be used in case of competing risk. The reproducibility of PET hypoxic regions will be evaluated as the proportion of overlapping voxels. Continuous endpoints will be analyzed with the *t*-test (Mann–Whitney-*U* test if not normal). Categorical endpoints will be analyzed with the Chi-squared test (Fisher’s exact test if the expected cell frequency is less than 5). Repeated measures will be analyzed by paired-samples *t*-test, Wilcoxon singed-rank test or mixed models.

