**Methods:**

The ESCALOX trial is a prospective randomized phase III study using cisplatin chemo-irradiation and the SIB-IMRT concept in patients with LAHNSCC of the oral cavity, oropharynx or hypopharynx to escalate the total dose to the GTV up to 80.5 Gy. Chemotherapy is planned either in the 1^st^ and 5^th^ week (cisplatin 20 mg/m^2^/d d 1–5 and d 29–33) or weekly (cisplatin 40 mg/m^2^/d) during RT. RT is delivered as SIB with total doses of 80.5 Gy/70.0 Gy/56.0 Gy with 2.3 Gy/2.0 Gy and 1.6 Gy in the experimental arm and in the control arm with 70.0 Gy/56.0 Gy with 2.0 Gy and 1.6 Gy. A pre-study with dose escalation up to 77.0 Gy/70.0 Gy/56.0 Gy with 2.2 Gy/2.0 Gy and 1.6 Gy is demanded by the German federal office of radiation protection (BfS). In the translational part of the trial 100 of the randomised patients will be investigated by 18-F-FMiso-PET-CT for the presence and behaviour of tumor hypoxia twice in the week before treatment start.

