## Background

Head and neck cancers are the seventh most frequent cancer in Germany (estimated incidence of 50/100.000 per year, Deutsche Krebsgesellschaft). The German Robert-Koch-Institut presented recently data on absolute disease numbers of all tumor entities. In 2013 for head and neck cancer there were 4.500 women and 13.000 men newly diagnosed in Germany [1]. For 2020 the new diagnosis expectations are higher: women 5.500 and men 14.300. Worldwide there are more than 550.000 new cases every year [2].

Head and neck cancers are representative for solid tumours in which new biological-imaging-based treatment strategies can be tested comparatively easily. This is true especially with regard to the impact of tumour volume, which correlates with cell number per tumour and tumor hypoxia, on response after non-surgical treatment.

Concomitant chemo-irradiation is superior to radiation alone in inoperable LAHNSCC. An absolute survival benefit of 8% at 5 years favouring chemo-irradiation was shown in the meta-analysis of the MACH-NC-group (2000) [3]. The up-date of the MACH- NC-group in 2009 included studies between 1994 and 2000. Again there was an absolute benefit of 6.5% for chemo-irradiation (independent of the setting – postoperative or primary chemo-irradiation) concerning the HR of death in comparison to local treatment alone [4]. In 2011 the MACH-NC group investigated the effect of chemo-irradiation in comparison to radiotherapy and revealed a 5-year absolute benefit (OS) due to concomitant chemotherapy for oral cavity: 8.9%, oropharynx: 8.1% and 4% for hypopharynx [5].

Besides tumor volume correlating with cell number per tumor, hypoxia is a further important biological parameter for tumor progression. Hypoxia increases radio-resistance and is a predictive factor for local failure. Hypoxia occurs in about 80% of head and neck tumors (primaries and/or lymph nodes). Based on experimental and clinical data, hypoxia is considered as a useful parameter for pre-therapeutic stratification in future randomized chemo-irradiation trials. More importantly, hypoxic sub-volumes of tumors are also evolving as target volumes for radiotherapy (“dose painting”) in some studies examining the significance of selective irradiation dose escalation. To investigate the shift of the hypoxic sub-volumes [18 F]-FMISO PET will be performed twice within 1 week before start of radiation treatment.

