Distinct dose response curves for radiotherapy have been calculated from clinical studies on head and neck cancer [20]. According to this data, one would expect an improvement of loco-regional control of an average 10% (range 6.9–40%) by a dose escalation of 10%. However, the available data are consistent with the hypothesis that the slope of dose response in large tumors is considerably shallower. The latter is likely related to the relatively larger hypoxic areas in large tumors [32, 33].

Generally, in head and neck tumours hypoxia plays a major role. In clinical radiation oncology it could be proven that hypoxia is correlated with a worse prognosis in especially in head and neck cancer [34–36].

Hypoxia reduces radiation- and chemo-sensitivity to a considerable extent as shown also in many experimental investigations. Using PET imaging and appropriate markers, hypoxia is found in about 80% of patients with advanced head and neck cancers [37, 38]. By using PET tracers which selectively concentrate in hypoxic cells (F-Miso) the visualization of hypoxic regions became possible [37, 39–44].

Retrospective data on head and neck cancer indicates that loco-regional control is already excellent with standard radio-chemotherapy if tumors without any sign of hypoxia on [18 F]-FMISO PET scans were treated. Lee et al. [45] showed for head and neck tumors with hypoxia detected by [18 F]-FMISO PET and treated using IMRT excellent loco-regional control (3y-LRPFS of 95%). Loco-regional control in head and neck tumors with significant enhancement in the [18 F]-FMISO PET was poor in a study by Thorwarth et al. [46]. Zips et al. showed a strong association for locally advanced head and neck cancer patients with stage III and IV of FMISO-image parameters and LPFS. The strongest association was seen for the PET investigations performed during week 1 and 2 of radiotherapy [47]. The stability of hypoxic tumor sub-volumes detected by FMISO-PET was investigated by Bittner et al. in 16 patients with LAHNSCC. They found in patients with hypoxic tumors in comparison between FMISO-PET 1 and 2 (two weeks apart) at the beginning of the radio-chemotherapy. In patients with persistent hypoxia after 2 weeks of treatment, the hypoxic sub-volumes showed relative geographical stable information [48].

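### Voxel overlap alone rises with the hypoxic fraction by chance, so it cannot on its own show that FMISO hypoxic regions are spatially stable

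*Protocol article*

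**What the plan says.** The Abstract (Methods) sets the size of the translational part: "100 of the randomised patients will be investigated by 18-F-FMiso-PET-CT". The Background gives the timing, "FMISO PET will be performed twice within 1 week before start of radiation treatment", and the purpose, which is to see whether hypoxic areas move between scans.

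The Secondary efficacy and safety endpoint analyses section then names one measure for this: "The reproducibility of PET hypoxic regions will be evaluated as the proportion of overlapping voxels". No other index is tied to PET reproducibility. The same section sets the status of the analysis: "Secondary efficacy and safety endpoints will be analyzed in an explorative manner on a 5% significance level".

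On how common hypoxia is, the Background says "Hypoxia occurs in about 80% of head and neck tumors (primaries and/or lymph nodes" and the Discussion says "hypoxia is found in about 80% of patients with advanced head and neck cancers". Neither section says what fraction of a hypoxic tumour is hypoxic.

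**The concern.** The paired scans ask a question about location: is the hypoxic part in the same place a few days later? A raw overlap proportion answers a mixture of two questions, how much of the tumour is hypoxic and whether the hypoxic part stays put. If half the tumour is hypoxic on each scan, considerable overlap arises even when the two patterns have nothing to do with each other.

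The Discussion expects hypoxic extent to differ between patients, since it links large tumours to relatively larger hypoxic areas. A table of overlap proportions could then partly rank patients by extent while being read as a ranking by stability. The Background describes hypoxic sub-volumes as emerging radiotherapy targets, so readers may use the figure to judge whether a single scan can define such a target.

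There is a second, smaller gap. The Discussion hypothesises that patients with marked FMISO enhancement gain more from dose escalation. For that, agreement between scans on whether a patient is hypoxic at all is relevant, and voxel overlap does not describe it.

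**Working it through.** The article states no expected value, target or precision for PET reproducibility, so there is no figure of its own to reproduce.

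**Inputs**
- Measure: overlap proportion, denominator not stated (Secondary efficacy and safety endpoint analyses).
- Patients: 100, scanned twice (Abstract, Methods; Background).
- Share with hypoxia: about 80% (Background; Discussion).
- Hypoxic fraction f of the tumour volume: not given. Assumed here to be 0.1 to 0.6 and equal on both scans.

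**Step 1: overlap expected from unrelated scans.** If each voxel is hypoxic with probability f on each scan, independently, the share hypoxic on both is f × f = f². Dividing by the share hypoxic on scan 1 (f) gives f. Dice gives 2f²/(2f) = f. Jaccard gives f²/(2f − f²) = f/(2−f). Over all tumour voxels it stays at f².

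| f | Over scan 1, or Dice | Jaccard | Over all tumour voxels |
|---|---|---|---|
| 0.1 | 0.10 | 0.053 | 0.01 |
| 0.3 | 0.30 | 0.176 | 0.09 |
| 0.6 | 0.60 | 0.429 | 0.36 |

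A simulation (20,000 voxels, 50 replicates) agrees: 0.100, 0.300 and 0.601 over scan 1, and 0.053, 0.177 and 0.430 for Jaccard. Kappa in the same simulation is 0.00 at all three fractions. Every denominator rises with f.

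**Step 2: one overlap, different agreement.** Let o be the overlap over scan 1 (or Dice). With equal fractions, observed voxel agreement is po = 1 − 2f(1−o), and chance agreement is pe = f² + (1−f)² = 1 − 2f(1−f). Then

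kappa = (po − pe)/(1 − pe) = 2f(o − f)/[2f(1 − f)] = (o − f)/(1 − f).

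At o = 0.60:
- f = 0.1: 0.50/0.90 = 0.56
- f = 0.3: 0.30/0.70 = 0.43
- f = 0.6: 0/0.40 = 0.00

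**Step 3: one agreement, different overlap.** Turned round, o = f + kappa × (1 − f), and Jaccard = o/(2 − o). At kappa = 0.5:

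| f | Dice | Jaccard |
|---|---|---|
| 0.05 | 0.525 | 0.356 |
| 0.2 | 0.60 | 0.429 |
| 0.4 | 0.70 | 0.538 |
| 0.6 | 0.80 | 0.667 |

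**Step 4: scans without a hypoxic voxel.** With N tumour voxels:

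| Situation | Over scan 1 | Dice or Jaccard | Over all tumour voxels |
|---|---|---|---|
| Both scans negative | 0/0 | 0/0 | 0/N = 0 |
| Only scan 1 hypoxic | 0 | 0 | 0 |
| Only scan 2 hypoxic | 0/0 | 0 | 0 |

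By the article's 80% figure, up to about 100 × (1 − 0.80) = 20 patients could be negative on both scans (95% binomial range 12 to 28).

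**The case against.** The best reply has four parts.

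- **Condensation.** The article spends one sentence on this. The denominator, the uptake threshold and the rule for empty regions commonly sit in the full protocol or analysis plan. That stands, and their absence is not held against the article. It does not answer the main point, because Step 1 shows the chance dependence under every denominator considered.
- **Overlap is the natural answer.** It says directly how much of the hypoxic region recurs in the same place, and it does respond to biology. The minimum possible overlap over scan 1 is max(0, 2f − 1)/f, which is zero for every f up to 0.5, so overlap there can run from 0 to 100%. This stands, and it is why overlap should be kept.
- **Kappa is not neutral.** It depends on the volume drawn around the hypoxic region. With o = 0.60 fixed, doubling the reference volume takes f from 0.30 to 0.15, and kappa from 0.43 to 0.45/0.85 = 0.53. This stands, and it argues against replacing overlap with kappa alone.
- **Low stakes.** The analysis is exploratory, and the boost volume is defined from the gross tumour and nodal size, not from FMISO. This stands too.

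A reader might infer that the measure is simply 0/0 for about a fifth of the patients. The article does not support that: it requires both scans to be negative and a hypoxic-voxel denominator that is nowhere stated. Tumours with no hypoxic region can also reasonably fall outside an analysis of hypoxic regions.

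**Conclusion.** The point holds as a limited one. The only reproducibility measure named for the paired scans mixes extent with stability, so on its own it cannot be compared between tumours of different hypoxic fraction or read as spatial stability. Over an assumed f of 10% to 60%, the same 60% overlap runs from a kappa of 0.56 down to 0.00. Between 10% and 30% the change is modest, 0.56 to 0.43; the extreme value arises only at the top of the range. Overlap alone also leaves agreement on hypoxia status undescribed for tumours negative on one or both scans.

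The figures rest on equal fractions on both scans, a chance benchmark that ignores position within the tumour, and assumed values of f.

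A reader might go further and infer that large tumours will look stable and small ones unstable whatever the biology, or that the PET result will be wrong. Neither is supported. The driver is the hypoxic fraction, not tumour size, and overlap reported beside that fraction is interpretable. The primary endpoint, the sample size and the safety rules are untouched.

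**What to change.** In the Secondary efficacy and safety endpoint analyses section, keep the overlap proportion and add, for each patient scanned twice:

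- the hypoxic fraction of the tumour on each scan;
- a chance-corrected agreement, namely voxel-wise kappa within the co-registered GTV at a fixed uptake threshold;
- the voxel-wise correlation of uptake between the two scans, which needs no threshold.

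Also report patient-level agreement (hypoxic or not on scan 1 against scan 2) across all patients scanned twice, so that double-negative and converting tumours are counted.

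The cost is a little more analysis of images already planned, with no further scan or patient. The downsides are a chance-corrected figure that will be lower than raw overlap, and kappa's dependence on how the GTV is drawn; the GTV used should be stated beside it.
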